### Implementation outcomes

Our project will focus on implementation outcomes as well as selected patient and provider outcomes for intended project goals. Success will be determined by adoption and effective use of the ACP approach within in-center as well as home dialysis settings. Patient and provider outcomes will be measured by the number of ACP conversations held and documented; POLST completed; the quality and fidelity of ACP conversation to the HIGHway process as taught during education sessions; provider evaluation of education activities in terms of impact on knowledge and skills; content, relevance, and significance of ACP intervention for patients, and SKD App usage.

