### Data collection

There are several distinct study populations for this study, with procedures and instruments for evaluation specific to each: 1) social workers/nurses participating in the training and implementation of intervention, 2) patients who agree to provide feedback on the advance care planning service they receive, 3) patients who agree to have an ACP session recorded.

Data on the number of ACP conversations conducted and the number of advance directives completed and filed in charts will be collected directly from the app for those teams that use it. In the alternative, sites that do not use the app will submit a brief weekly report via email with the number of ACP activities conducted that week as well as any successes or barriers encountered.

Fidelity check of the intervention will be performed by auditing a selection of the audiotapes of conversations between social works/nurses and patients to assess completeness of these conversations, to assess how adherent the visit was to the ACP checklist.

The anonymous survey for patients who attended an ACP session is based on previously validated Quality of Communication Scale, and adaptation of Patient Enablement Instrument. The survey’s purposes are to assess satisfaction with the ACP session, including change in confidence to complete ACP steps and quality of communication. Qualitative interviews of a sample of patients within dialysis center will be conducted to assess content, relevance and significance of ACP discussions based on a previously developed interview guide.

The implementation outcomes will be assessed through a survey to the participating social workers/nurses at the completion of their 9 months of participation. The questionnaire is based on the Workshop Evaluation Form (WEVAL). The questionnaire has been piloted with several social workers and adapted to the HIGHway project. Our main collection sources will be the evaluation questionnaires completed by the social workers or nurses, contingent on patients who consent to participate.

When an ACP conversation takes place, social worker/nurse will provide patient with an informational flyer about the project and a postcard with survey link. A Survey link will connect patient to a brief survey via Qualtrics (an encrypted survey system) regarding the conversation. Completion of survey will signify consent. The survey is anonymous.

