We plan to enroll 60 social workers or nurses total over the several training cohorts. The turnover and dropout are expected to be about 17%, resulting in target of 50 social workers/nurses who complete entire 9 months of training. The rational is the training capacity of the project. We expect that approximately 1,600 patients will receive ACP service because we will target each social worker/nurse conducting one ACP conversation per week during the 9 months of training, beginning after the first month. The proportion of patients who will participate in the post implementation survey is unknown. The target is 25% participation rate.

Quantitative analysis will be primarily descriptive, with descriptive statistics with confidence intervals to characterize survey responses on various questions. For several of the knowledge gain questions asked before and after the social workers engage in training, chi-square and t-tests will be used to assess change. Qualitative analysis will be used for both inductively and deductively assessing themes and subthemes. Given the short 2-year time frame for this project, and the proposed provision of ACP services to both seriously ill as well as stable dialysis patients, we have not tried to measure the impact of these activities on our end-users in terms of healthcare utilization or specific health outcomes or choices. Instead, the success of our ACP intervention—and receipt of goal-concordant care as the gold standard— is inferred from the high-quality communication based on our intervention, as demonstrated by the fidelity check of audiotaped ACP conversations and by patient survey responses. Further, we will measure the success of this implementation project by documenting that all ACP-related activities and discussions have taken place, by assessing the quality and completeness of GOC discussions, by mail-in survey of patients and family participating in discussions, and by qualitative interviews with selected patients.

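### The plan infers receipt of goal-concordant care from the quality of conversations, although no data source records the care received or compares it with patients' goals

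*Protocol article*

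**What the plan says.** The relevant text is in the last paragraph of Data collection in the protocol article. It gives two reasons for a limited scope: a two-year project, and a population that mixes seriously ill and stable patients. It then says "we have not tried to measure the impact of these activities on our end-users in terms of healthcare utilization or specific health outcomes or choices".

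The next sentence puts something in place of that measurement. Its subject is the success of the intervention, to which an aside adds "and receipt of goal-concordant care as the gold standard". Of this subject the article says that it "is inferred from the high-quality communication based on our intervention, as demonstrated by the fidelity check of audiotaped ACP conversations". The patient survey is then named as a second source for the same inference.

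Earlier in the same section the two sources named for this inference are described. Recordings are audited "to assess completeness of these conversations, to assess how adherent the visit was to the ACP checklist". The patient survey is meant to "assess satisfaction with the ACP session, including change in confidence to complete ACP steps and quality of communication", and it is anonymous.

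Under Implementation outcomes, success is tied to adoption and effective use of the approach. The measures listed there include the number of conversations and "POLST completed; the quality and fidelity of ACP conversation to the HIGHway process". Goal-concordant care is not in that list. It appears in Implementation strategy as the target of an adapted logic model (Fig. 2, not shown in the text available).

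**The concern.** Goal-concordant care has two parts: what the patient wanted, and what the patient then received. A statement that it was received needs information on both, for the same patients. The article disclaims the second part and then commits the project to inferring the whole.

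At stake is the scope of the eventual conclusion. If the project finds faithful, well-rated conversations, the plan as written lets it report that patients received care in line with their goals. The abstract's Discussion presents the project as a model for dialysis patients in the US that could change institutional policy, so readers may rely on such a statement.

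**Working it through.** No arithmetic decides this point. The article states no figure for goal concordance, so there is none to reproduce. The check is whether any listed data source observes care received, or its match with goals.

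| Source (section) | What it observes | Care received? | Match with goals? |
|---|---|---|---|
| Fidelity audit of recordings (Data collection) | Completeness of the conversation, adherence to the checklist | No | No |
| Anonymous patient survey (Data collection) | Satisfaction, change in confidence, quality of communication | No | No |
| Patient interviews (Data collection) | Content, relevance and significance of the discussions | No | No |
| Count of ACP conversations (Implementation outcomes; Data collection) | Activity | No | No |
| Count of advance directives filed (Data collection) | Forms completed | No | No |
| POLST completed (Implementation outcomes) | Orders completed | No | No |
| Social worker/nurse surveys (Table 1; Data collection) | Training, adoption into workflow, barriers, sustainability | No | No |
| App usage (Implementation outcomes) | Use of the tool | No | No |

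Of these eight sources, none observes care received and none observes the match.

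**Could the sources be combined?** The survey is anonymous, so as designed its answers cannot be joined to a patient's later care. Directives and POLST forms are the closest to care, but they record preferences or orders, not what was delivered. No follow-up of care after the conversation is described.

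**Could the link be taken from elsewhere?** The article points to an adapted logic model. That is a pathway from communication to concordant care. Using it as a premise does not test it, and the design described has no comparison or follow-up that would. The Background also reports that, among deceased participants of the earlier one-arm cohort who had an intervention meeting, 39% received hospice services against 24.8% overall in those centers, and 48% withdrew from dialysis before death. Those are rates of use. They do not show that the care matched each patient's goals, and that intervention was aimed at seriously ill patients, whereas HIGHway includes all patients in a center.

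**A check by example.** Take two centers with identical fidelity scores and identical survey results. In one, patients' stated goals are later followed; in the other they are not. Every data source in the table could read the same for both, so the plan would draw the same inference about receipt of goal-concordant care. The data separate good conversations from poor ones, but not honoured goals from unhonoured ones.

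**The case against.** The strongest defence is that this is an implementation project and says so. It openly leaves outcomes out, gives reasons, defines success by adoption and effective use, and plans a mainly descriptive analysis. Goal-concordant care is not an endpoint, a test or an estimand. The words at issue are an aside in a rationale for a surrogate, and the word for the step, inferred, is candid.

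Much of this stands. Leaving outcomes unmeasured is a legitimate choice of scope, and no one need ask for them to be added. But candour about the method does not remove the conclusion: the sentence still names receipt of care as something the project will infer. Nor is this a detail left to a fuller document. It is a positive statement, made directly after the text that rules out the measurement it would need.

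Several stronger readings are tempting, and the article does not support them:

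- **That the result is fixed in advance.** It is not. The inference depends on communication quality being shown, so poor fidelity or poor survey responses would defeat it.
- **That it rests on satisfaction alone.** The survey is based on a quality-of-communication scale and an adapted enablement instrument, and also covers confidence. These still describe the conversation.
- **That nothing measured bears on concordance at all.** Communication quality is a plausible precursor. The logic model figure and its source are not available here, so the strength of the link cannot be judged from the text. The accurate statement is that nothing measures care received or its match with goals.
- **That counting directives and POLST contradicts the statement that choices are not measured.** A count of completed forms is a process output. It need not record what patients chose, or any effect on those choices, so both statements can hold.
- **That the problem is thin coverage,** with one recording per worker and a 25% survey target. Recording every conversation and surveying every patient would leave care received just as unobserved, so coverage is not evidence for this point.

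**Conclusion.** The point holds as a fault in the stated conclusion. The article disclaims measurement of utilization, outcomes and choices, then infers receipt of goal-concordant care from sources that describe only the conversation.

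The fault is confined to one inference. Recruitment, the expected number of patients, the instruments and the descriptive analysis are untouched. Conclusions on adoption, fidelity and patient-rated communication are ones the planned data can address.

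This rests on two assumptions: that the data sources in the article are the complete set relevant to patients, and that receipt of goal-concordant care has its ordinary meaning of care delivered in line with the patient's goals. If a fuller document provides for observing later care against stated goals, the disclaimer in Data collection would itself need correcting.

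**What to change.** In the last paragraph of Data collection, delete "and receipt of goal-concordant care as the gold standard" from what is inferred. Add a sentence to this effect: the project draws conclusions on adoption, fidelity and patient-rated communication; goal-concordant care is a downstream aim under the logic model, is not measured, and no conclusion about it will be drawn.

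The cost is wording only, with no change to enrolment, instruments or analysis. The drawback is that the stated claim becomes more modest.

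Per-patient reporting of directives and POLST should not be made part of this fix. The app is optional, directive counts are described as coming from the app, and the article does not say that the weekly reports from other sites supply them. Such reporting could therefore require new data collection, and it would still not measure care received.

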## Discussion

Patients on dialysis want to discuss their preferences for treatment at the end of life (EOL) [16], but few do so [16, 17] and most nephrologists are reluctant or feel unprepared to lead such discussions [18, 19]. Effective tools are critically needed to elicit such preferences since over 50,000 Americans die of kidney disease annually, more than from breast or prostate cancer [20]. For dialysis patients with significant co-morbidities, risk of death within a year of starting dialysis is stark. Of those who had 4 or more comorbidities, 26% died within 30 days of dialysis initiation, and 60% died within a year [21]. These patients have higher – and often unwanted – intensity of care at EOL; in a four-year study of the United States Renal Data System, 49% of elderly long-term hemodialysis (HD) patients spent time in an intensive care unit in their final month of life, compared with 24% of cancer patients [22]. Further, nephrology clinicians think they understand their patients’ priorities, but a majority in one study were wrong about whether their patient [23]. The SDM-RSC intervention was designed to systematically elicit patient preferences for EOL care so that preference-concordant care could be provided.

Meaningful EOL conversations can change these outcomes and are associated with increased hospice referral, less aggressive and expensive medical treatment, and higher levels of family satisfaction. Yet less than 10% of ESRD patients report having a conversation about any EOL issues with their nephrologist in the previous year, although 90% said such conversations were important [14]. Few patients with ESRD engage in ACP, and the vast majority lack a written advance directive or surrogate decision maker, leaving them unprepared to provide guidance in medical decisions in a crisis [19–23].

By virtue of their willingness to voluntarily participate in this project, the dialysis center teams, especially the social workers, are likely to be more open to advance care planning than the average dialysis center staff member. Early adopters likely have different motivations than later adopters. The results of this project will be generalizable to others with an early adopter mindset. To achieve further spread beyond early adopters, other encouragements (such as introducing regulatory requirements) may be needed. Various barriers were evident in the implementation of the original intervention. To address these barriers will require enhanced social worker/nurse and inter-professional training; increased readiness and comfort discussing prognosis amongst dialysis team members; early engagement at all participant levels; and routinization of the process through policy change—all issues we plan to address in this larger implementation project.

Unanticipated barriers that may arise will be addressed by the project team using creative problem solving as a team, including getting input from the stakeholder engagement group, the dialysis organization advisory group, and the participating center teams. The management strategy of outlining the pros and cons of options for responding to barriers will be used to decide on optimal solutions to unanticipated problems.

The implementation of SDM-RSC rapidly scales the multimodal intervention to improve advanced care planning in dialysis centers across the US. The goal of this project will be to routinize advance care planning and make it an expected part of regular workflow in the care of patients undergoing dialysis.

## Data Availability

All data will be storage in a secure manner. They include storing identifiable data only in secure RedCap database at GW or Qualtrics tool (https://www.qualtrics.com (https://www.qualtrics.com/)) at MTPPI, limiting access to the secure database to specified research staff on the IRB maintained study list, only providing de identified data to others outside the study team as needed for data analysis, destroying data after period of maintaining data has elapsed in accordance with GW policies. MTPPI network security starts from authenticating any user. Also, documentation of security policies, procedures and access records, information technology record of all configuration settings on the components of the network are kept and maintained. The data that support the findings of this study are available from MTPPI but restrictions apply to the availability of these data, which were used under license for the current study, and so are not publicly available. Data are however available from the authors upon reasonable request and with permission of MTPPI. For the Application software tool, the data is stored on Amazon Web Services (AWS) platform. According to AWS privacy statement document, it is a HIPAA compliant secure platform. We will further ensure data privacy by validating through a professional evaluation of the site and oversight of data storage and usage activities.

## Abbreviations

HIGHway: Honoring Individuals Goals and Hopes: Implementing Advance Care Planning for Persons With Kidney Disease on Dialysis
SDM-RSC: Shared Decision Making-Renal Supportive Care
ACP: Advance care planning
SKC: Supportive Kidney Care
EOL: End of life
POLST: Physician orders for life sustaining treatment
PCORI: The Patient-Centered Outcomes Research Institute
ESRD: End of Stage Renal Disease
IRB: Institutional Review Board
KTA: Knowledge to Action
CFIR: Consolidated Framework for Implementation Research
WEVAL: Workshop Evaluation Form
HD: Hemodialysis
